### Survey analysis

The quantitative data from the CSQ will be analyzed using descriptive and correlational statistics. The CSQ contains several scales, providing composite scores that can be used to indicate differences in the secondary outcomes. Open ended questions will be analyzed through content analysis, focusing on key topics.

## Discussion

### Anticipated limitations

#### Changes in intention to conceive

Owing to our exclusion criteria, we will recruit only women who do not intend to conceive within the first year after enrollment. Nevertheless, in this study population with an anticipated mean age of 24 years, we fully anticipate that some women will change their intent to conceive over the first and subsequent study years. We will account for this in two ways. First we ask at each CSQ interview (3, 6, and 12 months) about the participant’s intent to conceive, and second, we will assume that randomization will distribute those who have intended pregnancies within the study period evenly to both arms of the study.

#### Expulsions

Most women will be aware when an IUD expulsion occurs 
[20], and should it occur, will make arrangements for alternative contraception. This alternative contraception may be a replacement device or a change in contraceptive method. Each participant will be provided with a toll-free number enabling them to contact the principal investigator ([name]) at any time. In addition, the study team will monitor follow-up visits, CSQs, government medical plan billings, and prescription records of alternative contraception prescribed or an IUD removed or inserted. In this manner, we believe we will be able to estimate device expulsion rate with a fair degree of accuracy. To reflect usual contraceptive conditions most accurately in the event of an expulsion, we are not providing a free replacement device. We have stratified at randomization for parity, as this may be a confounding factor in expulsion.

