The only copper IUDs available in Canada at the time this study began were the Nova-T (Nova-T200®; Bayer Inc, Canada), and two Flexi-T devices (Flexi-T300® and Flexi-T380(+)®; both Prosan International BV) 
[7]. Canadian physicians report higher rates of expulsion with the Flexi-T devices 
[6,15] and yet many prefer the Flexi-T380(+) because evidence supports copper devices with a surface area of 380 mm as being more effective than those with an area of 200 mm 
[10,14,16-19]. We found no reports in the literature describing the expulsion rates or effectiveness for the Flexi-T devices, although reported outcomes for NovaT200 are available 
[16-19].

This RCT will determine if the Flexi-T380(+) copper IUD (referred to hereafter as ‘FlexiT’) is comparable with the most common Canadian copper IUD currently in use, the NovaT-200 copper IUD (referred to as the ‘NovaT’), when placed immediately after a first-trimester abortion. Additionally, we will report the first rigorous evidence for the effectiveness of, and satisfaction with, the range of post-abortion contraceptive options available to Canadian women.

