### Sample-size justification for comparing expulsion rates for the NovaT and FlexiT

Our aim in this non-inferiority study is to provide evidence that the expulsion rate for the Flexi-T does not exceed that of the Nova-T by more than 10%. The rationale for this choice rests on the assumption that the detection rate for IUD expulsions is at least 85% 
[20], which implies that the loss in efficacy of a device due to expulsions is less than 0.15 times its expulsion rate, and correspondingly, that any difference in efficacy between devices is less than 0.15 times the difference in expulsion rates. Thus differences of 10% in expulsion rates translate into differences in efficacy of 1.5% or less.

We calculated power calculations for non-inferiority testing following the approach described by Blackwelder 
[21] using the on-line calculator provided by S. Patten 
[22].

Our null hypothesis is: H_0_: FlexiT expulsion rate ≥ NovaT expulsion rate + 10%.

This formula requires specification of the problem in terms of success proportions (that is, those not experiencing expulsion by 1 year). We will assume the rate of those not experiencing expulsion will be 96% for the Nova-T 
[17-19] and 92% for the Flexi-T. Thus, we require a sample size of 192 per group to attain 80% power at α = 0.05 to detect a difference in expulsion rates exceeding 10%. We will enroll a total of 400 women, a sufficient number to allow for changes to intention to leave the province and thus loss to follow-up using the health administrative databases. This recruitment will ensure the final sample is at least the 384 women required to test the null hypothesis that FlexiT has a significantly inferior (higher) expulsion rate compared with the NovaT.

Thus, our recruitment will include 400 women who choose to have IUDs and consent to be randomized to either the Flexi-T (200 women) or the Nova-T (200 women), and a further 200 who decide to not to use intrauterine contraception, who will be enrolled as a non-intervention comparator group. Therefore, a total of 600 women will be recruited.

The study clinic (see ‘Recruitment facility’, below) provides abortions to about 700 women meeting the entry criteria each year, and based on our previous research in this setting 
[23] we expect 40% of eligible women to choose an IUD, and 80% of these to enroll in IUD groups. Target enrollment is anticipated at 22 months.

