[27]), to maintain strict concealment. Staff will be kept unaware of the randomization design and of stratification factors involved, to mitigate the potential for unblinding of individual blocks. For women choosing an IUD, the study device determined by the randomization will be inserted by their surgeon immediately after the abortion and before the worman leaves the procedure or operating room. Blinding of the surgeon or the woman receiving the IUD is not possible, as the IUDs are distinct in appearance. Even once *in situ*, these two devices have a differing number and consistency of strings palpable at the cervical os. Following standard clinic protocol, all women will undergo PCR testing for chlamydia and gonorrhea before their abortion, and receive 2 g metronidazole as a single observed dose as prophylaxis against postoperative infection 
[28]. Women deemed to be at higher risk of a sexually transmitted infection (STI) 
[28] and those with positive PCR results will receive 1 g of azithromycin as well. A post-placement ultrasound image of the IUD *in situ* will be recorded.

Participants choosing no contraception and all other methods of contraception will receive normal instructions from the facility physician for implementation of their contraceptive method, undergo the same STI testing and prophylaxis protocol, and complete an intake CSQ before leaving the abortion facility.

Enrolled participants will complete the subsequent CSQ either by mail or as a web-based questionnaire at 3, 6, and 12 months post-abortion. User-friendly internet-based and paper-based formats are available for each of the four most common languages spoken in our study population.

All recruited women will receive reimbursement for their time in the form of a gift certificate at enrollment and for each completed CSQ submitted. In addition, women choosing to be randomized to an IUD arm will receive their device free of charge.

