### Analysis methods

Because our aim is to examine expulsion rates and establish the non-inferiority (within a margin of 10%) of the Flexi-T compared with the NovaT, the primary analysis will be based on an upper (one-sided) 95% confidence limit for the difference in expulsion rates (FlexiT rate minus NovaT rate). Non-inferiority will be inferred if the confidence limit value is less than 10%. This simple approach is valid so long as no systematic difference in follow-up occurs between groups. As a check, we will also conduct analysis to account for partial follow-up. Because our outcome definition is essentially composite and the relevant risk periods differ by components, Kaplan-Meier estimates for each component event will be determined, and composite estimates will be obtained by summing the estimated cumulative event rates (calculated as 1 minus the survival function) at the time points indicated in our operational definitions. Confidence intervals around the difference in these estimates will be calculated using the bootstrap method.

Rates for all secondary outcomes will be calculated in an ITT framework for events occurring within 1year and within successive years following the abortion, and for pregnancy events, those associated with a conception within a year or successive years. Outcomes will be determined using the CSQ, direct access to clinical follow-up visit records, and billing and procedure coding data from the administrative health-system databases. Multivariate logistic regression will be used to examine demographic, socioeconomic, and obstetric factors in relationship to primary and secondary objectives.

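### No masking of device type is stated for those who classify the primary expulsion outcome, although that step can be masked and about four to six reclassified women could change the conclusion

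*Protocol article*

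**What the plan says.** The article deals with blinding under Enrollment process: "Blinding of the surgeon or the woman receiving the IUD is not possible, as the IUDs are distinct in appearance". It adds that the strings differ even once the device is in place. The only masking of staff in that section concerns the randomisation design and the stratification factors, which protects allocation.

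Under Outcome determination, one-year expulsion comes from provincial administrative data and the contraception satisfaction questionnaire (CSQ). The data include removals, re-insertions and prescriptions for other contraception. The Expulsions paragraph of the Discussion has the study team monitor follow-up visits, CSQs, billings and prescription records, and concludes: "In this manner, we believe we will be able to estimate device expulsion rate with a fair degree of accuracy". Neither section says whether device type is hidden from whoever decides that a record is an expulsion.

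Analysis methods calls the outcome essentially composite and refers to operational definitions that the article does not print. The decision rule is there too: "the primary analysis will be based on an upper (one-sided) 95% confidence limit for the difference in expulsion rates", and "Non-inferiority will be inferred if the confidence limit value is less than 10" (per cent).

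On prior expectation, the Background says: "Canadian physicians report higher rates of expulsion with the Flexi-T devices". The same sentence goes on to say that many physicians prefer the Flexi-T380(+) because of its copper surface area. The sample-size section plans on more FlexiT expulsions: "We will assume the rate of those not experiencing expulsion will be 96% for the Nova-T" "and 92% for the Flexi-T".

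**The concern.** The reason given for not blinding, that the devices look and feel different, applies to the person inserting the device and the person wearing it. It does not apply to someone reading a record from which device information has been removed. The step that produces the primary endpoint can therefore be masked even though treatment cannot.

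Masking matters here because some of the sources are indirect. A re-insertion or a new contraceptive prescription can follow an expulsion, an elective removal or a change of method. If the reader knows the device, doubtful records may be resolved differently in the two arms. Such differential misclassification shifts the estimated difference itself. Randomisation does not protect against it, because it arises after allocation. The Kaplan-Meier and bootstrap check in Analysis methods addresses partial follow-up, not classification.

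Either error is possible. Over-calling FlexiT expulsions could make a non-inferior device fail. Under-calling them could support non-inferiority wrongly.

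**Working it through.** **Inputs, all from the article.** Expulsion 4% for NovaT and 8% for FlexiT (96% and 92% without expulsion), margin 10 percentage points, 80% power, 192 per group required, 200 per arm enrolled, upper one-sided 95% limit (z = 1.645).

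**The plan's own figure.** The article states: "we require a sample size of 192 per group to attain 80% power at" α = 0.05. With unpooled variance,

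n = (z₀.₉₅ + z₀.₈₀)² × [0.96×0.04 + 0.92×0.08] / (0.10 − 0.04)² = (1.645 + 0.842)² × 0.112 / 0.0036 ≈ 192.3.

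This reproduces 192 (power at 192 is 79.9%). A one-sided 0.025 would need 245, so the plan uses one-sided 0.05, in line with its decision rule.

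**Sensitivity of the decision at 200 per arm.** The Wald limit is

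U = p_F − p_N + 1.645 × √[p_F(1 − p_F)/200 + p_N(1 − p_N)/200].

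At the planned counts (16 and 8): 0.04 + 1.645 × √[(0.0736 + 0.0384)/200] = 0.04 + 1.645 × 0.02366 = 7.89%.

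With four more FlexiT women counted as expelled (20 and 8): 0.06 + 1.645 × √[(0.0900 + 0.0384)/200] = 0.06 + 1.645 × 0.02534 = 10.17%.

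With NovaT held at 8/200:

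| FlexiT expelled | Wald | Newcombe | Score |
|---|---|---|---|
| 16 | 7.89% | 8.13% | 8.18% |
| 17 | 8.46% | 8.70% | 8.75% |
| 18 | 9.03% | 9.27% | 9.33% |
| 19 | 9.60% | 9.83% | 9.89% |
| 20 | 10.17% | 10.40% | 10.46% |

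All three methods cross 10% at the fourth woman, who completes 4/200 = 2% of the arm. Read upward, the table gives the opposite error: if the true counts were 20 and 8, missing one FlexiT expulsion would bring the Wald limit from 10.17% to 9.60% and pass the rule.

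**Other mixes.**
- 200 per arm, only NovaT expulsions removed: Wald 9.96% at five and 10.36% at six. Newcombe (10.35%) and score (10.41%) cross at five.
- 200 per arm, two added to FlexiT and two removed from NovaT: Wald 9.88%, still a pass; Newcombe 10.16% and score 10.22%. A third FlexiT woman takes Wald to 10.45%.
- 192 per arm, 15 against 8: four added gives Wald 9.99%, so a fifth is needed (10.58%).
- 192 per arm, 15 against 7 or 16 against 8: four added gives Wald 10.44% or 10.58%. By Newcombe or score, three already suffice in these two cases (10.10% to 10.29%).

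By the Wald limit the range is four to six women.

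**The case against.** The strongest objection is that this is silence in a condensed article. Assessor masking is often left to the full protocol, and the operational definitions mentioned under Analysis methods may be mechanical enough to leave little discretion. Part of this stands: masked or rule-based classification may already exist. But the article chooses to discuss blinding and outcome ascertainment, and gives a reason for not blinding that does not cover this step. A written definition may narrow discretion, but it does not mask the person applying it to a doubtful record.

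A reader might infer that the study team, or the investigator whom women can telephone, will classify with the device in view. The article does not say so. It says that the team monitors sources and that a telephone line exists. It does not say who classifies or what that person sees.

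A reader might also infer that bias will run against FlexiT. The Background reports higher expulsion and a preference for FlexiT in the same sentence, and the stated aim of the trial is to show non-inferiority. The direction is open.

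Finally, any trial with an expected limit of 7.89% against a 10% margin turns on a few events, so the arithmetic measures fragility, not bias. That is right. The article gives no number of ambiguous records, and it expects most women to notice an expulsion, which may keep that number small.

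**Conclusion.** The point holds as a design improvement that should be made. It is not a demonstrated bias. No masking of device type is stated for the classification that creates the primary endpoint, and the reason given for not blinding does not extend to it.

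The size is four FlexiT women moved from non-expulsion to expulsion, assuming 200 per arm and exactly the planned 16 and 8 events. Other mixes, or 192 per arm, need about four to six by Wald. It would go too far to say that four doubtful records decide the trial: that requires all four to be in one arm, moved in one direction, at exactly the planned counts.

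Confidence is moderate, because the full protocol and the operational definitions are not shown. If masked classification is already in place, one sentence saying so settles the matter.

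**What to change.** Have existing study staff apply the operational definitions to extracts from which device name, arm and string description have been removed. Lock each woman's classification before it is linked to the allocation list. Flag records in which the text reveals the device, and records in which expulsion remains ambiguous.

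Keep all randomised women in this analysis. Repeat the primary upper limit twice, first counting every ambiguous record as an expulsion and then counting every one as a non-expulsion. Do not drop women because their text names the device, since that would select after randomisation and possibly unequally by arm. Both repeats treat the arms alike, so they show dependence on the rule for ambiguous records; protection against arm-specific judgement comes from the masking.

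The cost is redaction time and a lock step, with no extra assessor or visit. Enrolment was still open at publication, so the step can be in place before one-year outcomes are complete; any records already classified can be re-read from redacted extracts. Two limits remain: masking of free text will be incomplete, and reporting by women who know their device is not corrected.

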#### Contribution

This is the first study to determine the expulsion rate for the FlexiT380(+) IUD, and to determine if it is non-inferior to the standard IUD available in Canada, the Nova-T 200, for post-abortion contraception. In addition, this study will provide the first ITT evidence on outcomes for a wide range of contraceptive methods currently available in Canada, including consumer satisfaction, method continuation, and pregnancy rates at 1 year post-abortion. Understanding of satisfaction and effectiveness for common contraceptive options will better inform efforts to prevent recurrent unintended pregnancy among Canadian women.

## Trial status

This trial is currently open for enrollment, with the first enrollments having commenced on 5 October 2010. Enrollment in the non-intervention group (those women not choosing to use an IUD) has been slower than expected but full enrollment is anticipated in late 2012.

## Abbreviations

BC0: British Columbia a province in Canada; CSQ: Contraception satisfaction questionnaires; FlexiT380 and Flexi T: Copper Intrauterine Device (“Flexi-T380(+)”® Prosan, The Netherlands); IUD: Intrauterine device; NovaT200 and NovaT: Copper Intrauterine Device (“Nova-T200”® Bayer Inc, Canada); PCR: Polymerase chain reaction; RCT: Randomized controlled trial; UBC: University of British Columbia; WHRI: Women’s health research institute.
